# ABSTRACT

Artekin is an artemisinin-based fixed-dose antimalarial drug combination developed in the 1990s in China. The active components are dihydroartemisinin and piperaquine. Piperaquine is a bisquinoline compound originally synthesized in France with high *in vitro* activity in the nanomolar range against multidrug resistant *Plasmodium falciparum*. Piperaquine has been used as monotherapy in China for over two decades. It has proved to be generally very well tolerated and effective although resistance to the monotherapy has developed until the early 1990s prompting its reformulation in combination with other drugs, including dihydroartemisinin. Dihydroartemisinin has already been extensively evaluated and shown to be safe – with no major identifiable adverse effects. The combination has become widely used in South East Asia and is now registered in Cambodia, China and Vietnam.

Several factors make this combination a promising development: Artekin is a fixed-dose co-formulation used as a once daily 3-day regimen, and this may improve adherence and ease of drug administration in comparison for instance to the more complex regimens of artemether-lumefantrine (Coartem©). It is also inexpensive in comparison with other artemisinin-based combination chemotherapies, e.g. Coartem© or artesunate-mefloquine with an estimated cost per adult treatment of approximately 1 USD. Finally, preliminary clinical trials of this treatment in more than 5,000 patients carried out in South East Asia have shown it to be well tolerated and highly effective on par with Coartem© and artesunate-mefloquine in areas of high-level multi-drug resistance of *P. falciparum*.

This study is part of a multicentre phase III trial aimed at evaluating the safety and efficacy of the newly manufactured GMP batch of Artekin in 1,500 African children with uncomplicated *P. falciparum* malaria. In Kilifi, 500 patients aged 6-59 months with uncomplicated *P. falciparum* malaria will be randomly allocated to receive either dihydroartemisinin-piperaquine or artemether-lumefantrine. The objective of the study is to evaluate the efficacy and safety of dihydroartemisinin-piperaquine and to demonstrate that dihydroartemisinin-piperaquine (1) is at least as effective as artemether-lumefantrine and (2) cures at least 90% of treated patients.

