# OBJECTIVES

## Primary objectives:

The primary objective of the study is to measure the day 28, PCR-corrected cure ratios of dihydroartemisinin-piperaquine and artemether-lumefantrine and demonstrate that:

- The cure ratio of dihydroartemisinin-piperaquine is non-inferior to that of artemether-lumefantrine (non-inferiority margin = 5%);
- The cure ratio of dihydroartemisinin-piperaquine is at least 90%.

This cure ratio is defined as the proportion of evaluable patients with adequate clinical and parasitological response at day 28.

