### Sample size calculation

The study is designed as a non-inferiority trial.

The opinion of physicians and experts in malaria treatment has been sought for defining the non-inferiority margin, and this has been set at 5%. In addition, the experts have agreed that, in order for the new treatment to be considered efficacious, its PCR-corrected cure ratio at day 28 should not be lower than 90%. Therefore, in the present trial, dihydroartemisinin-piperaquine will be considered efficacious if both the following conditions are met (see section 2.1):

(i) The PCR-corrected cure ratio at day 28 of dihydroartemisinin-piperaquine is not inferior to the cure rate of artemether-lumefantrine by 5% or more, and independently of the reference drug performance,

(ii) The cure rate of dihydroartemisinin-piperaquine is at least 90%.

In summary, for the non-inferiority analysis, the clinical and statistical specifications for the sample size computations are as follows:

- Primary end point = PCR-corrected cure ratio at day 28.
- Primary analysis = based on 97.5% one-sided confidence intervals for the difference in day 28 cure ratios.
- Alpha = 0.025 (one-sided).
- Power = 80%.
- Cure ratio at day 28 of artemether-lumefantrine = 95% (results from multicentre phase III trial of Coartem in children; [name] personal communication).
- Non-inferiority margin for the difference (test-reference) = -0.05%.
- Analysis will be per-protocol.

To demonstrate non-inferiority of Artekin compared to Coartem the study will require 235 patients per treatment group. To allow for an approximate 5% loss to follow-up rate, 250 patients per treatment group (500 patients in total) will be enrolled in the Kilifi study.

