### Prohibited Medications

Any antimalarial, or antibiotic with antimalarial activity (erythromycin and other macrolides, co-trimoxazole and other sulphonamides, any tetracycline (including doxycycline, and quinolones). Intake of such drugs will lead to the withdrawal of the patient from the study and classification as treatment failure in the intention-to-treat population.

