## Analysis Populations

### Modified Intention to Treat (ITT) Population

Defined as the ITT population with the exclusion of the lost-to-follow-up patients before Day 28 for unknown reasons (non informative drop-outs). More specifically, patients withdrawing from the study for reasons 7 will be excluded, while all other withdrawals will be counted as failures (these reasons might be considered potentially correlated with lack of efficacy, i.e. are referred to as informative drop-outs).

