### Per Protocol (PP) Population (or Evaluable Population)

Defined as all randomized patients who will be eligible according to the study protocol, received at least 80% of the study medication, will not take other anti-malarial drugs and, in case of the presence of asexual parasite stages on thick or thin blood smears, will have an evaluable PCR analysis.

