## Statistical Analysis

### Primary end point analysis

The primary analysis will be based on a 97.5% (one-sided) confidence interval (CI) computed on the difference between the 28-day PCR corrected cure ratios (PP population) of the test and the reference treatments, respectively.

In order to claim that dihydroartemisinin-piperaquine is efficacious, the lower limit of the 97.5% confidence interval of the difference between the treatment groups must be >-0.05 and the point estimate for the 28-day PCR corrected cure ratio of dihydroartemisinin-piperaquine must be >0.90%, in the PP population.

All patients withdrawn from the study will be considered as failures in the ITT population (worst-case scenario).

For computing the PCR-corrected cure ratio, the following rules will be applied:

- The patients with reappearing asexual parasitaemia, which are subsequently found to be due to re-infections are considered as treatment success in both PP and ITT populations;
- The patients for whom the PCR analysis is not interpretable (or blood sample unavailable) are considered as treatment failure in the ITT population, but are excluded from the PP population.

Robustness of results for the primary end point will be investigated by using other analyses, such as the survival analysis techniques.

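### The PP and evaluable definitions that carry both efficacy conditions can drop children who failed treatment, and no ITT result bears on the claim

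*Protocol*

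**What the plan says.** All references are to the protocol.

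- **Decision rule (12.3.1).** Efficacy is claimed if "the lower limit of the 97.5% confidence interval of the difference between the treatment groups must be >-0.05" and if the point estimate for dihydroartemisinin-piperaquine "must be >0.90%, in the PP population" (evidently meaning 90%). Section 9.1 agrees: "This cure ratio is defined as the proportion of evaluable patients with adequate clinical and parasitological response at day 28". So does section 10.4.2: "Analysis will be per-protocol".
- **PP population (12.2.2).** Among other conditions, a child must have "received at least 80% of the study medication, will not take other anti-malarial drugs". No exception is given for treatment failure.
- **Evaluable patients (12.2.3, under the safety population heading).** A child counts if parasite counts run to the analysis day, or if the child stopped because parasites reappeared and PCR showed recrudescence.
- **Withdrawal reasons (10.8.2).** Reason 1 is any treatment failure, early failures included. Reason 3 is antimalarial use, limited to use outside the protocol.
- **Rescue (11.3.3).** Early and late failures in both arms receive another antimalarial.
- **ITT-type rules.** Section 12.2.1 leaves out loss to follow-up (reason 7) and counts all other withdrawals as failures, because "these reasons might be considered potentially correlated with lack of efficacy, i.e. are referred to as informative drop-outs". Section 11.2.2 attaches "classification as treatment failure in the intention-to-treat population" to prohibited drugs. Sections 12.2.3 and 12.3.1 instead count every withdrawn child as a failure in ITT.

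**The concern.** A primary cure ratio must keep its failures in the denominator. Here a child who fails is withdrawn, is given another antimalarial and may not have finished the study drug. Each of these facts can remove the child from the population in which both conditions are judged. If that happens, the cure ratio rises in each arm, and the 90% condition, a single-arm figure, is easier to meet even when the losses are balanced. If more failures are dropped on the test drug, the difference also moves toward non-inferiority.

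A second, lesser matter concerns the other withdrawals that the protocol regards as possibly related to lack of efficacy. They are counted as failures in ITT, but no wording says what follows if ITT and PP disagree. A claim could stand on PP while the ITT result missed the margin.

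**Working it through.** **1. Following a failure through the definitions.**

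- *Early failure, for example danger signs with parasitaemia on day 1 (11.3.1).* The child is withdrawn under reason 1 and rescued. Under 12.2.2 the rescue drug is another antimalarial, and the child may also have had under 80% of study drug. Under 12.2.3 there are no counts to day 28, and the event is not a reappearance confirmed as recrudescent. The child is lost on both definitions.
- *Late failure with PCR-confirmed recrudescence.* Under 12.2.3 the child stays evaluable. Under 12.2.2, read literally, the rescue drug excludes the child. The two definitions disagree.
- Taken to its end, the literal wording of 12.2.2 removes every rescued failure, leaving a cure ratio of 100% by construction. That cannot be intended.

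**2. Size of the effect when failures are dropped.** Inputs: 235 evaluable per arm and 95% cure (10.4.2). The number of failures dropped is assumed.

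- 95% of 235 is about 223 cured and 12 failures: 223/235 = 94.9%.
- One failure dropped: 223/234 = 95.3%. Two dropped: 223/233 = 95.7%. Each is worth about 0.4 points, against a margin of 5.
- Near the threshold: 211/235 = 89.8% does not meet 90%. With one failure dropped, 211/234 = 90.2% does.

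**3. Other informative withdrawals, illustration only.** The documents give no counts, so 10 (test) and 5 (reference) out of 250 per arm are assumed, with no loss to follow-up and about 95% cure in those kept. The lower limit is d - 1.96 × sqrt[p1(1-p1)/n1 + p2(1-p2)/n2].

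| Handling of excluded children | Test | Reference | Difference (points) | Lower limit (points) |
|---|---|---|---|---|
| Excluded (PP) | 228/240 = 95.0% | 233/245 = 95.1% | -0.1 | -4.0, met |
| Included, 80% cured | 236/250 = 94.4% | 237/250 = 94.8% | -0.4 | -4.4, met |
| Included, 50% cured | 233/250 = 93.2% | 235.5/250 = 94.2% | -1.0 | -5.3, missed |
| Included, none cured | 228/250 = 91.2% | 233/250 = 93.2% | -2.0 | -6.7, missed |

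The standard error is 1.97 points in the first row and 2.40 in the last, so part of the change in the limit is extra variance. The difference itself moves by 2.0 - 0.1 = 1.9 points.

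**4. Cost of involving an ITT-type population.** Assume 95% true cure among children kept, equal arms and 4% informative withdrawal in each arm. Power for the non-inferiority condition is Φ(0.05/SE - 1.96).

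- PP, 240 per arm at 95%: SE = sqrt(2 × 0.95 × 0.05/240) = 0.0199, power about 71%.
- Modified ITT, 250 per arm at 0.96 × 95% = 91.2%: SE = sqrt(2 × 0.912 × 0.088/250) = 0.0253, power about 51%.

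The PP figure is already below the planned 80%. With equal 95% cure and one-sided alpha 0.025, the usual formula gives (1.96 + 0.84)² × 2 × 0.95 × 0.05/0.05², or 299 per group, not 235. That is a separate matter.

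**The case against.** PP is a usual primary population for non-inferiority, and the protocol names it consistently in 9.1, 10.4.2 and 12.3.1. The abstract's wording that the drug "cures at least 90% of treated patients" does not override the objective. ITT cure ratios are planned with stated failure rules, so a discordant result would be visible. Choosing PP is therefore not the error.

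Section 10.8.2 limits the antimalarial reason to use outside the protocol, and treatment failure is not itself a listed PP exclusion. Read with 12.2.3, late recrudescent failures were very probably meant to stay in as failures. This softens the problem in 12.2.2. It does not repair 12.2.3 for early failures, nor the 80% dose condition for a child whose treatment stopped because it was failing. Directly observed dosing, with redosing after vomiting, should keep incomplete treatment uncommon.

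Two stronger readings are tempting and not supported. A reader might take the 1.9 points as the bias of the PP analysis. It assumes that no excluded child was cured, while 12.3.1 itself presents its all-fail rule as a worst case and 12.2.1 says only that the reasons may be related to efficacy. Prohibited drugs include antibiotics that may be given for unrelated infections. A reader might also set the 15 children per arm between 235 and 250 against the 90% condition: 223/250 = 89.2%. But that allowance is for loss to follow-up, which modified ITT excludes, so the ratio there stays at 223/235 = 94.9%. The documents plan no rate of informative withdrawal.

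**Conclusion.** The point holds in two parts. First, 12.2.2 and 12.2.3 are wrong as written: taken literally, early treatment failures, and under 12.2.2 any rescued failure, can leave the population in which both conditions are judged. Each failure dropped adds about 0.4 points to an arm's cure ratio at 235 per arm and 95% cure. How many would be dropped depends on how the wording is applied, which the protocol does not settle.

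Second, the claim rule is silent on disagreement between PP and ITT. The 10 versus 5 example shows that disagreement is possible (-4.0 versus -6.7 points), on assumed counts and with zero cure among excluded children. At 80% cure among them, the claim would still be met. The documents do not show that disagreement is likely.

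**What to change.** **(a) Sections 12.2.2 and 12.2.3.** State that a child who meets a treatment-failure definition before or when stopping study drug, or before or when receiving another antimalarial, stays in the PP/evaluable population as a failure. State that only antimalarials taken outside the protocol, and not given for treatment failure, lead to exclusion. Make the two definitions agree. This costs a few sentences and needs no new data.

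**(b) Section 12.3.1.** First reconcile which ITT rule governs: modified ITT (12.2.1) or every withdrawn child as a failure (12.2.3 and 12.3.1). Then state that efficacy is claimed without qualification only if the result in that population is consistent with PP, and define consistent in advance. The analysis is already planned, but the chance of an unqualified claim falls. If consistent means meeting the same margin, power for that condition drops from about 71% to about 51% in the 4% withdrawal example. The protocol should state this loss.

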# NULL HYPOTHESIS

Dihydroartemisinin-piperaquine is non-inferior to artemether-lumefantrine in the treatment of paediatric patients aged 6 to 59 months with uncomplicated *P. falciparum* malaria as assessed by clinical and parasitological cure on day 28.

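### Three statements in the primary-analysis specification are wrong as printed: the 0.90% cure threshold, the -0.05% margin in the sample-size inputs, and a null hypothesis that states non-inferiority

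*Protocol*

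**What the plan says.** **Success rule (section 12.3.1).** There are two conditions, both in the per-protocol population. The first is that "the lower limit of the 97.5% confidence interval of the difference between the treatment groups must be >-0.05", written as a proportion without a percent sign. The second is that "the point estimate for the 28-day PCR corrected cure ratio of dihydroartemisinin-piperaquine must be >0.90%, in the PP population".

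**Margin.** Section 9.1 asks that the new drug be "non-inferior to that of artemether-lumefantrine (non-inferiority margin = 5" percent. The text of section 10.4.2 says that expert opinion was sought for "defining the non-inferiority margin, and this has been set at 5" percent. The input list in that same section then reads "Non-inferiority margin for the difference (test-reference) = -0.05", followed by a percent sign.

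**Absolute cure threshold.** Section 9.1 lists, among the things to be demonstrated, "The cure ratio of dihydroartemisinin-piperaquine is at least 90" percent. Condition (ii) of section 10.4.2 says "The cure rate of dihydroartemisinin-piperaquine is at least 90" percent. The Abstract also gives 90%.

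**Hypothesis.** The whole of section 8, headed as the null hypothesis, is one sentence that begins "Dihydroartemisinin-piperaquine is non-inferior to artemether-lumefantrine in the treatment of paediatric patients aged 6 to 59 months".

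**The concern.** A reader should be able to apply a prespecified success rule without guessing at the units. Here one decision threshold and one formal design input each combine a proportion with a percent sign, which makes each 100 times too small. The sentence labelled as the null hypothesis is what the trial hopes to conclude, so it is the alternative hypothesis of a non-inferiority test.

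The wording of the 90% objective also does not match its rule. To demonstrate that the cure ratio is at least 90% is a statement about the true ratio. A point estimate above 90% is a statement about the sample.

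The Kilifi data are to have their own statistical analysis (section 10.2), and the protocol calls the study pivotal and expects it to supply registration data (section 16). Any later analysis document could copy these lines as they stand.

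**Working it through.** **Inputs.** From section 10.4.2: 235 evaluable per group, reference cure ratio 95%, one-sided alpha 0.025, power 80%. Assumption: the true test-arm cure ratio equals the reference at 95% for the sample-size check, because the protocol states no test-arm figure.

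**1. Which margin lies behind the 235?** With unpooled variance, n per group = (z_alpha + z_beta)² × 2 × 0.95 × 0.05 / margin².

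| Margin | One-sided alpha 0.05 | One-sided alpha 0.025 (as stated) |
|---|---|---|
| 0.05 | 235 | 299 |
| 0.0005 (-0.05% read literally) | 2,349,372 | 2,982,575 |

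The planned 235 belongs to a margin of about 5 percentage points. The printed -0.05% did not enter the calculation. (That 235 matches alpha 0.05 and not the stated 0.025 is a separate matter, and nothing below depends on it.)

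**2. The cure threshold, literal and intended, at n = 235.**
- Above 0.90%: 0.009 × 235 = 2.1, so 3 cures pass. The exact binomial probability of 3 or more cures exceeds 0.999 even at a true cure ratio of 5%.
- Above 90%: 0.90 × 235 = 211.5, so 212 cures are needed.

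**3. The hypothesis.** Section 8 makes non-inferiority the null. Condition (i) in section 10.4.2 and the rule in section 12.3.1 claim it only when the lower confidence limit excludes a deficit of 5 points. That is a test of H0: cure(DP) − cure(AL) ≤ −0.05 against H1: > −0.05. Section 8 therefore conflicts with both.

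**4. The point-estimate condition with the unit corrected.** Exact binomial probability of 212 or more cures in 235:

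| True cure ratio, test drug | Passes the 90% condition alone |
|---|---|
| 88% | 17% |
| 89% | 32% |
| 90% | 51% |
| 95% | 99.9% |

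At the smallest passing result, 212/235 = 90.2%, the lower 97.5% Wilson limit is about 85.7%.

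Success also needs the non-inferiority condition. Summing over all outcomes with 235 per group and a Wald lower 97.5% limit for the difference gives:

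| True test cure | True reference cure | Meets both conditions |
|---|---|---|
| 90% | 95% | about 3% |
| 89% | 95% | about 1% |
| 88% | 95% | about 0.4% |
| 90% | 90% | about 37% |

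**The case against.** The strongest reply is that these are slips of the pen which the protocol itself resolves. The margin is 5% in section 9.1 and in the text of section 10.4.2, and -0.05 in section 12.3.1. The threshold is 90% in the Abstract, in section 9.1 and twice in section 10.4.2. No trialist would take 0.9% as the intended cure threshold. This stands as an argument about consequence: the design is recoverable, and a reader of the whole protocol would apply it correctly. It does not make the lines right. One is half of the operative success rule and another is a formal design input.

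A reader might go further and infer that the whole success rule is meaningless, that the trial's test is reversed, or that the design calls for millions of patients. The documents support none of these. The confidence-interval condition is correctly written and can fail, so the joint rule can fail even with the misprint. The -0.05% stands only in the sample-size inputs. The reversal is confined to the one sentence of section 8, and nothing in the protocol says that failing to reject that sentence would support the drug.

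On the point estimate, the fair objection is that the 51% pass rate describes one condition in isolation. With the reference at the protocol's 95%, the non-inferiority condition holds the joint rate to about 3% at a true cure ratio of 90%. That answer depends on a strong reference. If both drugs cure 90%, the joint rate is about 37%, although section 10.4.2 says that the 90% condition holds independently of how the reference performs. A lower-limit test would be a trade-off for the sponsor to weigh, and its absence is not an error. What remains is that the word *demonstrate* promises more than a point estimate delivers.

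**Conclusion.** The point holds as three misstatements and one mismatch of wording. The cure threshold in section 12.3.1 and the margin in the inputs of section 10.4.2 are each printed 100 times too small, and section 8 states the alternative as the null. Taken literally, the cure condition could hardly fail (3 cures of 235, where 212 are meant). Read with the rest of the protocol, the intended design is clear, the operative test runs in the right direction, and neither the sample size nor the inference changes once the lines are corrected.

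The mismatch over *demonstrate* remains after the units are corrected. Its size depends on the reference: joint success at a true cure ratio of 90% is about 3% with a 95% reference and about 37% with a 90% reference. These figures assume 235 evaluable per group, independent binomial outcomes and a Wald limit, since the protocol does not name the interval method.

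**What to change.** - Section 12.3.1: write the second threshold as >0.90 (90%).
- Section 10.4.2, input list: write the margin as -0.05 (-5 percentage points).
- Section 8: restate as H0: cure(DP) − cure(AL) ≤ −0.05 against H1: cure(DP) − cure(AL) > −0.05, for the day 28 PCR-corrected cure ratio.
- Abstract, section 9.1 and condition (ii) of section 10.4.2: word the second criterion as an observed cure ratio above 90%, reported with its 95% CI, and keep *demonstrate* for the non-inferiority comparison.

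The cost is a few sentences in a protocol amendment. Sample size, power and the confidence-interval condition are unaffected. If the sponsor does want to demonstrate 90%, the rule would have to rest on a lower confidence limit, which is harder to meet than the point estimate. That is a design choice to be made deliberately, and these corrections do not require it.

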## Outcome measures and sample size.

### End points

#### Primary end point

The primary end point will be the PCR-corrected adequate clinical and parasitological response (PCR corrected ACPR) at day 28.

ACPR is defined as the absence of parasitaemia on day 28 irrespective of the axillary temperature without previously meeting any of the criteria of early treatment failure or late clinical or parasitological failure.

Patients with late asexual parasite reappearance will be considered ACPR if the PCR analysis shows a new infection rather than a recrudescence.

The total treatment failure is defined according to the WHO criteria [25] as the sum of early and late treatment failures (for definitions see chapter 7.3 Treatment failure).

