### Safety population

All subjects who have received any dose of the study medication will be included in the safety population. The analysis of the 28 and 63-day cure ratios will be performed both for the intention-to-treat (ITT) patient population (all randomised patients) and the evaluable patient population. Patients are evaluable for the analysis of the 28 and 63-day cure ratios if parasite counts are recorded up to Day 28 and 63 or the patient discontinues due to reappearance of *P. falciparum* confirmed by PCR genotyping to be recrudescent.

The ITT analysis also includes patients who discontinue before Days 28 and 63 due to other reasons. These patients will be counted in the ITT analysis as treatment failures regardless of their reason for discontinuation.

Safety and tolerability measurements will be summarised for the ITT patient population.

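### For children who discontinue before Day 28 (or 63), sections 12.2.3 and 12.3.1 classify PCR-confirmed re-infections in incompatible ways, and 12.2.3 read literally also removes early treatment failures from the evaluable set

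*Protocol*

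**What the plan says.** **Re-infection as success.** Protocol 10.4.1.1 (Primary end point): "Patients with late asexual parasite reappearance will be considered ACPR if the PCR analysis shows a new infection rather than a recrudescence". Section 12.3.1 (Primary end point analysis) repeats this for the PCR-corrected ratio: recurrences "which are subsequently found to be due to re-infections are considered as treatment success in both PP and ITT populations". Section 12.2.2, which defines the Per Protocol (or Evaluable) Population, is consistent with it. For a child with parasites it asks only that the child "in case of the presence of asexual parasite stages on thick or thin blood smears, will have an evaluable PCR analysis".

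**The competing rule.** Section 12.2.3, headed Safety population, contains a second definition of evaluable: "Patients are evaluable for the analysis of the 28 and 63-day cure ratios if parasite counts are recorded up to Day 28 and 63", or if "the patient discontinues due to reappearance of *P. falciparum* confirmed by PCR genotyping to be recrudescent". Of those who stop early for any other reason it says: "These patients will be counted in the ITT analysis as treatment failures regardless of their reason for discontinuation".

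**Further ITT rules.** Section 12.3.1 also states: "All patients withdrawn from the study will be considered as failures in the ITT population (worst-case scenario". Section 12.2.1 sets a modified ITT population that leaves out losses to follow-up before Day 28 and counts all other withdrawals as failures.

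**Who is withdrawn.** Section 10.8.2 lists any treatment failure, early failures included, as a reason to stop treatment or to exclude the patient from further efficacy assessment. Late clinical failure (11.3.2.1) requires parasitaemia with fever between day 4 and day 28, with no PCR condition. Late parasitological failure (11.3.2.2) requires PCR-proven recrudescence.

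**The concern.** The same child can be a success, a failure or absent from the analysis, depending on which paragraph the analyst follows. The conflict reaches the primary analysis set, because 12.2.2 uses PP and evaluable as names for one population and 12.2.3 applies its own evaluability rule to the day-28 cure ratio.

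Two distortions could follow. First, new infections before day 28 are likely to differ by arm: the protocol gives piperaquine a half-life of about 14 days and plans to estimate its chemoprophylactic effect. Counting discontinued re-infections as ITT failures would turn a prophylactic difference into an apparent cure difference in favour of the test drug. Second, an evaluable set that admits early stoppers only after PCR-proven recrudescence loses early treatment failures, who are true failures. The trial is open label, so these rules should not be left to be settled after outcomes are known.

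**Working it through.** **Step 1: apply each rule to the same children.**

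| Child | 10.4.1.1, 12.2.2 and the re-infection rule of 12.3.1 | 12.2.3 |
|---|---|---|
| New infection, counts recorded to Day 28 | success in PP and ITT | evaluable; not an ITT failure by its discontinuation rule |
| New infection with fever on day 21, withdrawn | success in PP and ITT | not evaluable; ITT failure |
| PCR-confirmed recrudescence, withdrawn | failure in PP and ITT | evaluable failure; ITT failure |
| Early treatment failure, withdrawn by day 3, no counts to Day 28 | failure in PP and ITT | not evaluable; ITT failure |

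The conflict is in rows 2 and 4. Row 2 will occur: a febrile re-infection on days 4 to 28 meets the late clinical failure definition and so the first withdrawal reason in 10.8.2. For row 2 the withdrawn-patient sentence in 12.3.1 also gives ITT failure, so 12.3.1 contradicts itself.

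**Step 2: size of the re-infection effect.** No stated figure can be reproduced here. The protocol gives only about 50 breakthrough infections over follow-up, recrudescent or new, and no day-28 rate by arm. Assume true failure c = 5% in both arms, re-infection r, and that every re-infected child discontinues before Day 28.

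- 12.3.1 re-infection rule: cure = 1 − c
- 12.2.3 ITT: cure = 1 − c − r
- 12.2.3 evaluable: cure = (1 − c − r)/(1 − r)

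| r, reference/test | 12.3.1 difference | 12.2.3 ITT, test vs reference | 12.2.3 evaluable, test vs reference |
|---|---|---|---|
| 5/2% | 0 | 93% vs 90%: +3 | 94.9% vs 94.7%: +0.2 |
| 10/3% | 0 | 92% vs 85%: +7 | 94.8% vs 94.4%: +0.4 |
| 15/5% | 0 | 90% vs 80%: +10 | 94.7% vs 94.1%: +0.6 |

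The ITT shift equals the between-arm difference in re-infections that lead to discontinuation. If half of the re-infected children in each arm discontinue, +7 becomes +3.5; if none do, it is 0.

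**Step 3: effect on the confidence limit.** Take 250 per arm and the lower limit d − 1.96 × √[p₁(1−p₁)/n₁ + p₀(1−p₀)/n₀], to be compared with −5 points. Assume 20 test and 12 reference failures, and 5 and 25 re-infections that discontinue.

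- 12.3.1 re-infection rule: 230/250 = 92.0% vs 238/250 = 95.2%; d = −3.2, limit −7.5 (margin missed).
- 12.2.3 evaluable: 225/245 = 91.8% vs 213/225 = 94.7%; d = −2.8, limit −7.3 (missed).
- 12.2.3 ITT: 225/250 = 90.0% vs 213/250 = 85.2%; d = +4.8, limit −1.0 (met).

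**Step 4: early failures dropped from the evaluable set.** Same failures, no re-infections, starting from the limit of −7.5.

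- 5 of the 20 test failures early, none in the reference arm: 230/245 = 93.9%; d = −1.3, limit −5.3 (missed).
- 10 of the 20 early, none in the reference arm: 230/240 = 95.8%; d = +0.6, limit −3.0 (met).
- Half early in both arms (10 of 20 and 6 of 12): 230/240 = 95.8% vs 238/244 = 97.5%; d = −1.7, standard error 1.63, limit −1.7 − 1.96 × 1.63 = −4.9 (just met).

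**The case against.** The best defence is that the intended rule is clear. The rule in 12.3.1 is written for computing the PCR-corrected ratio, 10.4.1.1 agrees, and the section that actually defines the PP population keeps re-infected children in. The outlier is text under a safety heading. That shows which reading was meant, but it does not remove the other: 12.2.3 names the day-28 cure ratio and both populations, and the withdrawn-patient sentence stands inside 12.3.1 itself.

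A reader might infer that all re-infected children become non-evaluable and ITT failures under 12.2.3. The text does not support that. A child with counts to Day 28 is unaffected, including one whose new infection first appears on that day. Re-infection is not itself a withdrawal reason, and an afebrile re-infection is not a late parasitological failure. The affected group is mainly the febrile re-infections.

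A reader might also set +3 to +10 points against the 5-point margin as if the primary conclusion were at risk by that amount. That range is an upper bound, and it falls in ITT, whereas both success criteria are judged in PP.

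On early failures, the objection is partly right. Section 12.2.2 does not exclude them, the violations in 10.8.2 that remove patients from the evaluable set do not include treatment failure, and 10.4.1.1 counts them in total failure. They also remain ITT failures. Safety follow-up to day 42 could supply counts to Day 28 for some of them. The loss therefore depends on reading 12.2.3 literally, but that is what it says.

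**Conclusion.** The contradiction is real and limited to children who discontinue before Day 28 (or 63). For PCR-confirmed re-infections it can change the ITT result, and in one assumed case it reverses whether the ITT limit clears the margin. It moves the primary PP difference by less than about 1 point. The larger risk to the primary analysis is the literal loss of early treatment failures from the evaluable set. In the assumed cases that takes the lower limit from −7.5 to between −5.3 and −3.0 points, the latter only if half of 20 test-arm failures are early and none in the reference arm are.

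All re-infection, failure and early-failure counts are assumptions. The documents do not show how often these children will occur, so the calculations show what the choice of paragraph could do, not what it will do. The plan should still be corrected, because following one of its stated rules can give a wrong primary population.

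**What to change.** Delete the evaluability and ITT sentences from 12.2.3, leaving only the safety population there. Keep one definition each of PP and ITT, reconciling 12.2.1, 12.2.2, 12.2.3 and 12.3.1, and state that:

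- a recurrence with a PCR-confirmed new infection, febrile or not, is a success for the PCR-corrected day-28 cure ratio in PP and ITT, whether or not the child discontinues;
- early treatment failures and PCR-confirmed recrudescences, whether late clinical or late parasitological failures, stay in PP as failures;
- the sentence in 12.3.1 that makes all withdrawn patients ITT failures excepts PCR-confirmed re-infections.

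The PCR condition has to be explicit for late clinical failure; otherwise a febrile re-infection remains both a failure and a success. The day-63 ratio, which 12.2.3 also covers, needs the matching rule. The cost is wording only, with no new data or visits.
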